## Abstract

**Background:**

Binge eating disorder (BED) is a common and disabling problem associated with impaired cognitive control. Preliminary studies show that brain-directed treatments, including transcranial direct current stimulation (tDCS) and attention bias modification training (ABMT), improve cognitive control and alleviate symptoms of BED. When combined, tDCS may enhance the effects of ABMT, and vice versa, thereby improving treatment outcomes.

**Methods:**

This protocol describes a feasibility single-blind randomized sham-controlled trial of concurrent self-administered tDCS and ABMT in adults with BED (The TANDEM Trial). Eighty adults with BED will be randomly assigned to one of four groups: ABMT with real or sham self-administered tDCS, ABMT only, or waiting list control. In the treatment arms, participants will complete 10-sessions of their allocated intervention over 2–3 weeks. Outcomes will be assessed at baseline (T0), immediately post treatment (T1), and 6 weeks after end of treatment (T2), and at comparable timepoints for participants in the waitlist control group. Feasibility will be evaluated by assessing recruitment/retention rates and blinding success. Acceptability will be assessed quantitatively *via* participant ratings and qualitatively *via* semi-structured interviews. Episodes of binge eating at follow-up will be the primary clinical outcome and rate ratios from Poisson regression will be reported. Secondary outcomes will assess changes in ED and general psychopathology, attention bias toward high calorie foods, and executive function.

**Discussion:**

It is hoped that data from the trial will contribute to the development of neurobiologically informed treatments for BED, provide insights into the potential use of at-home variants of tDCS, and inform the design of future large scale trials.

## Introduction

Binge eating disorder (BED) is a common and disabling eating disorder (ED) affecting 1–3% of the global population (1). It is characterized by recurrent episodes of binge eating accompanied by feelings of loss of control and subsequent distress. Episodes occur in the absence of compensatory behaviors intended to prevent weight gain (2). Among individuals with BED, psychiatric and physical health comorbidities are common; nearly 80% of those diagnosed with BED will suffer from another psychiatric disorder during their lifetime (3), and up to 88% live with overweight or obesity, increasing individual risk for obesity related physical health problems (4). Consequently, the economic and quality of life burden associated with BED is substantial (5–7).

Psychotherapy [particularly cognitive behavior therapy (CBT)] and self-help interventions are recommended first-line treatments for BED (1). However, only about half of those who complete treatment report a significant reduction in, or abstinence from, binge eating in the 12-months following the end of treatment: moreover, neither treatment yields a significant or sustained reduction in weight (8). With respect to pharmacotherapy, second-generation antidepressants, anticonvulsants, and central nervous system stimulants produce short-term reductions in episodes of binge eating and are routinely used when treating BED. However, drug-driven reductions in binge eating episodes are not sustained beyond 3–6 months. Lisdexamphetamine, a central nervous system stimulant, is the only drug approved for use in the treatment of moderate-severe BED. However, the effect of the drug on ED psychopathology and mood remains unclear, and data on the long-term maintenance of effects are lacking. There are also significant risks associated with the drug's use; little is known about the effects of long-term administration, and rates of adverse events and premature discontinuation of the drug were elevated in RCTs (4, 8). It is possible that combining psychotherapy with pharmacotherapy may produce superior outcomes from treatment, however, findings from a recent meta-analysis yielded minimal support for this hypothesis; of the 12 included trials, only two reported that combined treatment enhanced binge eating and weight outcomes, both of which used anticonvulsant medications, and only two reported modest improvements in weight loss, but not binge eating, outcomes, both of which used the weight-loss medication, Orlistat (9).

It is widely agreed that novel treatments informed by neurobiological models of illness are needed (10). Current models propose that emotion dysregulation, elevated food cue reactivity, and executive dysfunction, are central to the etiology and maintenance of BED (11–16). These difficulties may indicate a broad impairment in cognitive control, and therefore aberrant functioning of the brain's cognitive control network. Cognitive control is the ability to orchestrate thought and action in accordance with internal goals and relies on prefrontal brain regions (e.g., the dorsolateral prefrontal cortex [dlPFC]) and associated neural networks (17). In this framework, the affective reactivity (i.e., craving and emotional reactivity) and poor self-regulatory abilities reported in BED may be a consequence of impairments in cognitive control, and interventions which improve cognitive control may facilitate remission from BED.

Cognitive bias modification (CBM) is one tool which may be used to improve cognitive control. CBM refers to a class of interventions that use experimental paradigms to change biased cognitive processes which perpetuate maladaptive behavior (18). Attention bias modification training (ABMT) is a form of CBM which aims to alter the automatic allocation of attention toward salient cues. Food-specific variants of ABMT, which were developed for use in binge-type EDs and obesity, train individuals to avoid salient high-calorie food cues and attend to neutral and low-calorie food cues (19). Meta-analyses of RCTs in healthy volunteers have revealed that a single session of food-specific ABMT is associated with a significant short-term reduction in high-calorie food consumption (medium effect size) (20) and a significant short-term reduction in bias toward high-calorie foods (medium effect size) (21). Though few studies have used food-specific ABMT in BED, those that have report promising outcomes from treatment. One study reported that a single session of ABMT was associated with a significant short-term reduction in subjective food craving (22). Another open feasibility trial delivered 8 weekly sessions of ABMT and reported significant post-treatment reductions in weight, ED symptoms, episodes of binge eating, and attention bias toward food, and these were sustained to 3-month follow-up (23). Thus, although data on the long-term effects of ABMT are lacking, the available evidence suggests that ABMT may improve affective regulation in the context of food (i.e., cognitive control), and may have clinical utility in BED.

Non-invasive brain stimulation (NIBS) may also be used to modify functioning of cortical regions or networks implicated in BED (24, 25). Transcranial direct current stimulation (tDCS) is a NIBS technique which may be particularly well-suited to the treatment of BED: it is a safe and well-tolerated technique which is inexpensive, portable, easy to use, and suitable for remote self-administration (26, 27). In tDCS, a constant weak direct current is applied *via* electrodes placed on the scalp to increase (anodal tDCS) or decrease (cathodal tDCS) cortical excitability. Specifically, tDCS modulates network dynamics within functionally connected areas beyond the cortical regions located beneath the electrodes. As a result, tDCS has the potential to modulate task- or symptom-specific neural networks. These changes in cortical excitability outlast the stimulation period (up to 60 min after a single-session) and, with repeated administration, may lead to lasting changes in brain function (26). In light of this, tDCS is being applied to the treatment of psychiatric disorders with moderate success, particularly in major depression (26). However, questions remain about optimal participant/patient selection, parameters for stimulation, mechanisms of action and the effects of long-term use.

Proof-of-concept studies suggest that tDCS may be effective for the treatment of binge-type EDs. In bulimia nervosa, a proof-of-concept RCT with 24-h follow-up, indicated that a single-session of right dlPFC anodal tDCS improves ED psychopathology, reduces craving for food, reduces urge to binge, and improves self-regulatory control during reward related decision making (28). In BED, a single-session RCT using right dlPFC anodal tDCS reported a short term reduction in craving for food and desire to binge eat in participants who received real tDCS (29). This finding was replicated in a sham-controlled crossover trial: following a single-session of right dlPFC anodal tDCS, short-term improvements in food-related response inhibition and craving for food were observed in participants who received real 2mA tDCS stimulation, as opposed to real-1mA or sham stimulation (30).

Two studies have examined the effect of multiple sessions of tDCS on BED symptoms. A randomized sham-controlled trial involving 32 adults examined the effect of 10 sessions of tDCS on attention bias toward food, craving for food, and cognitive flexibility (31). In this trial, tDCS was given with the anode over the left dlPFC and the cathode over the right dlPFC (2mA/20 min). Sessions were 3/week until 10 sessions had been completed. At post-treatment and 45 day follow up, real tDCS treatment was associated with a greater reduction in attention bias toward food, a greater reduction in craving for food, and an improvement in cognitive flexibility. However, effect sizes were small, and the authors acknowledged several study limitations, including a small sample (*n* = 32) and concerns about the effect of poor eye-tracker calibration on the reliability of attention bias outcomes.

Our group has also recently completed an RCT of six sessions of right-anodal tDCS targeting the dlPFC delivered over 3 weeks in adults with BED [*n* = 65, (32) for protocol]. In this trial, we examined whether symptoms of BED were improved by an intervention involving the concurrent delivery of tDCS and approach bias modification training, a form of CBM which targets approach bias toward high-calorie foods. Participants were randomly allocated to one of three study groups (approach bias modification training with real tDCS, approach bias modification training with sham tDCS, or wait-list control) and outcomes were assessed at baseline, 3-weeks post-randomization, and 7-weeks post randomization. Clinical and neurocognitive outcomes are yet to be published; however, findings from a qualitative study of the treatment experience indicate that this combined approach to treatment is tolerable and acceptable (33).

It has been suggested that the efficacy of tDCS may depend on the functional state of the brain at the time of stimulation. If this is true, then greater and longer-lasting neuroplastic effects might be achieved when tDCS and CBM co-activate a disorder-related neural network (34). This may be because, by altering the relationship between excitatory (glutamatergic) and inhibitory (GABAergic) systems in the brain (35), tDCS creates optimal conditions for memory reconsolidation, a process which may re-enforce the new learning which takes place during CBM. Similarly, CBM promotes the activation of disorder relevant brain areas, and this might enhance the effectiveness of stimulation. Consistent with this, several studies in anxiety, depression, and substance abuse disorders have reported superior outcomes from treatment when tDCS was combined with interventions which activate cognitive control regions (27, 36–38).

In summary, concurrent tDCS and food-specific CBM may be a promising treatment, or adjunct to treatment, for BED. This is because of (a) evidence suggesting that tDCS and food-specific CBM may independently produce therapeutic effects in BED, and (b) the neurobiological rationale for combining these two treatments. Moreover, with the recent arrival of tDCS devices intended for supervised self-administration, both interventions can now be safely provided in the home, thereby increasing their accessibility and scalability. Accordingly, we present the protocol for a feasibility randomized controlled trial of concurrent at-home self-administered tDCS and food-specific ABMT in BED (The TANDEM trial).

## Study aims

The primary aim of the TANDEM trial is to assess the feasibility of using 10 sessions of concurrent food-specific ABMT (henceforth, ABMT) and self-administered right-dlPFC anodal tDCS as a treatment for BED. This intervention will be compared to training in combination with sham stimulation, stand-alone training, and a “no treatment” waiting control condition. In doing so, we aim to acquire key information to inform the design of a large-scale RCT.

Specifically, we aim to:
estimate the rate ratio for the proposed primary outcome, change in the number of monthly episodes of binge eating from baseline to follow up. This will inform the sample size calculation for a large-scale RCT.explore the feasibility of conducting a large-scale RCT of at-home self-administered concurrent tDCS and ABMT in adults with BED by assessing recruitment, attendance, and retention rates;assess acceptability by examining participant ratings of treatment acceptability and tolerance, and by evaluating feedback provided during semi-structured interviews;determine the best instruments for measuring primary and secondary outcomes in a full trial by examining the quality, completeness, and variability in the data.

The primary clinical endpoint will be the change in monthly episodes of binge eating from baseline to follow-up. Secondary aims will focus on evaluating changes in overall ED pathology and general psychopathology, changes in attention bias toward high-calorie foods, and changes in executive functioning from baseline to 6-weeks post treatment completion.

## Methods

Reporting of this protocol is guided by the Standard Protocol Items: Recommendations for Interventional Trials (SPIRIT) checklist (39) and the Consolidated Standards of Reporting Trials (CONSORT) statement extension for feasibility randomized controlled trials (40). The TANDEM trial has also been registered with the U.S. National Institute for Health (NIH) Clinical Trials database (ClinicalTrials.gov; trial identifier: NCT04424745).

### Study design

TANDEM is a randomized single-blind sham-controlled feasibility trial with four parallel arms: [ABMT + real tDCS], [ABMT + sham tDCS], [ABMT only], and 8-week wait-list control. After baseline assessment (T0), participants will be randomly allocated to a study group. Those allocated to treatment groups will then complete 10 sessions of their allocated treatment over 2 weeks. Outcome measures will be completed first at baseline (T0), then again immediately after completing treatment or after 2-weeks waiting (T1), and finally 6-weeks after completing treatment, or after 8-weeks of waiting (T2). Process outcomes will also be assessed at each treatment session.

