### Intervention

Participants will complete 10 sessions of tele-supervised treatment over 2–3 weeks (i.e., week daily sessions until 10 sessions have been completed). Sessions will involve either concurrent ABMT and real/sham tDCS, or ABMT only. Participants in the waiting control arm will receive ABMT after completion of the T2 assessment.

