### Trial procedure

The individual participant timeline is illustrated in Figure 3. Study duration for each participant is 8 weeks. All participants will partake in assessments at each of the three time points; baseline (T0), post-treatment (T1) and follow-up (T2). Each assessment will be completed *via* videoconferencing (i.e., participants complete both assessments and treatment at home using a laptop or desktop computer with a webcam). Questionnaire measures will be completed online using Qualtrics^XM^ and neurocognitive tasks will be completed online using either Gorilla^TM^ or Millisecond by Inquisit^TM^.

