**Figure 3 F3:**
[figure not shown]
TANDEM participant timeline.

Informed consent will be provided *via* an online consent form (Qualtrics^XM^). Once completed, potential participants will be screened over the phone for inclusion in the study. At screening, BED diagnosis is confirmed using a standardized interview [Eating Disorders Diagnostic Screen; (47)]. Physical and psychiatric comorbidities, current medications, and tDCS safety are assessed using a general health questionnaire developed for the purpose of screening. Eligible participants then complete the baseline (T0) assessment. After baseline assessment, participants are randomized to one of four groups: (1) ABMT + real tDCS, (2) ABMT + sham tDCS, (3) ABMT only, or (4) wait-list control group. Intervention groups will then complete 10 sessions of treatment, up to 5 sessions/week, across 2–3 weeks. The waitlist control group will receive no experimental treatment during this time. All participants will complete the post-treatment assessment (T1) after the 10^th^ (final) session of treatment or 2-weeks of waiting, and the follow-up assessment (T2) 6-weeks after completing treatment, or after 8-weeks of waiting. After completing the final (T2) follow-up, waiting control participants will receive ABMT.

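### Treated participants who need more than 2 weeks for their 10 sessions can be assessed up to 1 week later than waitlist controls, which contradicts the stated 8-week duration and can slightly favour treatment in waitlist contrasts

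*Protocol article*

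**What the plan says.** **Visit timing.** The Study design section of the protocol article places the assessments "immediately after completing treatment or after 2-weeks waiting (T1), and finally 6-weeks after completing treatment, or after 8-weeks of waiting (T2"). The Trial procedure section repeats the rule: "after the 10^th^ (final) session of treatment or 2-weeks of waiting, and the follow-up assessment (T2) 6-weeks after completing treatment, or after 8-weeks of waiting". In the three treated arms the visits therefore follow the end of treatment. In the waitlist arm they are fixed.

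**Treatment duration.** Study design says that treated participants "complete 10 sessions of their allocated treatment over 2 weeks". Three other places give a longer window:
- Abstract, Methods: "participants will complete 10-sessions of their allocated intervention over 2–3 weeks"
- Intervention: "Participants will complete 10 sessions of tele-supervised treatment over 2–3 weeks"
- Trial procedure: "Intervention groups will then complete 10 sessions of treatment, up to 5 sessions/week, across 2–3 weeks"

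**Overall duration and comparability.** Trial procedure states: "Study duration for each participant is 8 weeks". The Abstract says outcomes are taken at the post-treatment visits "and at comparable timepoints for participants in the waitlist control group".

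**Use of the visits.** The primary clinical outcome is the change in monthly binge episodes from T0 to T2 (Primary outcomes). The Data analysis section makes the interactions of time with treatment at T1 and T2 the primary parameters. Study aims and Primary outcomes both say that the rate ratio will inform the sample size of a larger trial.

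**The concern.** A treated participant who needs a third week moves both visits back by up to a week. No waitlist participant moves. An analysis by nominal visit treats T1 and T2 as the same time in every arm, so for late finishers it compares slightly different lengths of follow-up.

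If binge eating declines on its own after entry, the later-assessed arm gains some of that decline, and a waitlist contrast counts it as benefit. At stake is the waitlist rate ratio for the primary clinical outcome, one of the figures that may be carried into a later sample size calculation. A rate ratio pushed away from 1 would make that trial too small.

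The duration statements also disagree with each other, whatever the size of any bias.

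**Working it through.** **Step 1: reproduce the 8 weeks.** Let D be the treatment duration in weeks. Treated T1 = D and treated T2 = D + 6. Waitlist T1 = 2 and T2 = 8. The offset at each visit is D − 2. This counts treatment and waiting from the same starting point.

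| D (weeks) | Treated T1 | Treated T2 | Offset from waitlist |
|---|---|---|---|
| 2 | 2 | 8 | 0 |
| 2.5 | 2.5 | 8.5 | 0.5 |
| 3 | 3 | 9 | 1 |

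The stated 8 weeks is reproduced at D = 2 and at no other value in the 2–3 week range. The largest offset is 1/2 = 50% of the waitlist T1 interval and 1/8 = 12.5% of the waitlist T2 interval.

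**Step 2: who is affected, and in which direction.** Sessions run on weekdays, at most five per week. Ten sessions with none missed span 12 calendar days from a Monday start and 14 from any other weekday. A participant with full attendance has no lag and could be assessed at most about 2 days early. Missed sessions can only push completion later. The lag therefore runs almost entirely one way, but only for those who exceed 2 weeks.

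**Step 3: effect on the T2 rate ratio with no treatment effect.** The document gives no background rate of change, so the weekly decline d is an assumption. If the rate falls by a constant proportion d per week, a one-month recall window that ends L weeks later has its mean rate multiplied by (1 − d)^L. With no treatment effect this is the rate ratio against waitlist.

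| d per week (assumed) | L = 0.5 | L = 1 |
|---|---|---|
| 1% | 0.995 | 0.99 |
| 3% | 0.985 | 0.97 |
| 5% | 0.975 | 0.95 |
| 8% | 0.959 | 0.92 |
| 10% | 0.949 | 0.90 |

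These figures give every treated participant the same lag. If half finish on time and half are a full week late, d = 3% gives (1 + 0.97)/2 = 0.985 and d = 8% gives (1 + 0.92)/2 = 0.96.

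**Step 4: the T1 window.** The outcome is a monthly count. Taking a month as four weeks, a count at week 2 covers two weeks before baseline (2/4 = one half), and a count at week 3 covers one such week (1/4). Late finishers and waitlist controls would thus mix different amounts of pre-baseline time at T1. At T2 both windows lie wholly after baseline.

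**Step 5: what this could do to a later sample size.** For illustration, assume a true rate ratio of 0.80 against waitlist, d = 5%, and a sample size roughly proportional to 1/(log rate ratio)².
- Full one-week lag for everyone: 0.80 × 0.95 = 0.76, and (ln 0.80 / ln 0.76)² = (0.223/0.274)² ≈ 0.66. The trial would be about one third too small.
- Half-week average lag: 0.80 × 0.975 = 0.78, and (0.223/0.248)² ≈ 0.81. It would be about one fifth too small.

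The first case is an upper bound within the stated window for these assumed values. Neither applies if the later trial is sized on real against sham stimulation.

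**The case against.** **The schedules can be read as equal.** Under Study design they coincide exactly, and daily weekday sessions with none missed finish within 14 days. A reader might infer that treated participants as a group are assessed later than their controls. The text does not support that: only those who run past 2 weeks are late, and the document does not say how many that will be. This stands, and it limits the point to a lag of 0 to 1 week for some participants.

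**A longer lag is not documented.** A reader might add time for equipment delivery and training and arrive at two weeks or more. The Safety procedures section does mention training and an ability check before treatment. However, no gap between T0 and the first session is stated, nor the day from which waiting time is counted, and the timeline figure is not available. A start delay would widen the lag if waiting runs from T0 or randomisation, but that is an assumption and is not counted here.

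**The bias is conditional.** The 3–8% weekly decline has no source in the document. Improvement after entry may be concentrated early, which would leave less drift by weeks 8–9. The mechanism is symptom change over time. It is not shown to apply to the neurocognitive tasks, four of which are not measured at T2. This also stands.

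**Comparable need not mean identical.** Weeks 8 and 8–9 can fairly be called comparable, so that statement is weakened and not false. The 8-week duration might be nominal, but it is stated for each participant and does not hold for anyone who takes longer than 2 weeks.

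**This is a feasibility trial.** P-values are exploratory, arms have about 20 participants, and a shift of a few per cent is likely small against sampling error. That makes the consequence modest. It does not remove it, because a systematic shift is carried forward if the waitlist estimate is used for planning.

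**Anchoring to the end of treatment is legitimate.** T1 and T2 are defined as post-treatment visits. Fixing all arms to randomisation would put a two-week T1 in mid-treatment for slower participants. This stands and shapes the fix.

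**Conclusion.** The point holds in a limited form. The protocol gives two treatment durations and two visit clocks that agree only under the shorter one. Treated visits can fall at weeks 3 and 9 against 2 and 8 in the waitlist, contrary to the 8-week duration stated for each participant. That part is arithmetic on the protocol's own text.

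The effect on the waitlist rate ratio depends on an assumed background decline and on how many participants run late. At 3–8% per week it is at most 0.97–0.92 at T2, and about 0.985–0.96 if half are a full week late. The direction would favour treatment.

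A reader might infer that the estimated effect of stimulation is distorted too. It is not: real tDCS, sham tDCS and ABMT only follow one timing rule, so contrasts among them are unaffected by this mismatch. The matter should be corrected, but it does not undermine the trial's feasibility aims.

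**What to change.** 1. Reconcile the 2-week, 2–3-week and 8-week statements across the Abstract, Study design, Intervention and Trial procedure sections. The sponsor must say which duration applies.
2. Keep the treated-arm visits tied to the end of treatment, and match waitlist T1 and T2 dates to the treated participants' actual timing. State the day from which waiting time is counted.
3. Recruitment ended in February 2022 and data collection was due to finish by June 2022, so for data already collected:
   - report days from randomisation to T1 and T2 by arm;
   - account for actual assessment time in the waitlist contrasts. Waitlist visits are fixed at 2 and 8 weeks, so a comparison at week 9 relies on an extrapolated trend, and that assumption should be stated;
   - qualify the waitlist rate ratio before using it to size a larger trial.

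**Cost.** Text corrections and a little more analysis. With matched dates, waitlist visits vary slightly and some of those participants would wait up to a week longer for T2. No additional participants or measurements are needed.
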